## STUDY PROCEDURES

Refer to Appendix I for Study Procedures and Visits Table. Refer to Appendix II for Laboratory Specimens Collection, Timing and Distribution Table.

Note that at study initiation, a pilot study will be conducted with up to 100 participants. For these participants, all study procedures as outlined below will be followed EXCEPT for the study product allocation. Pilot participants will undergo mock randomization as all participants in the pilot phase will receive 5 days of active drug. The purpose of this pilot study is to ensure study feasibility, safety and conduct prior to allocating study product based on randomization. Participants in the study pilot will not be informed of the mock randomization process or that they all received active drug. Concealing this will allow study staff to evaluate procedures and participant compliance in a situation that exactly mirrors that of the clinical trial. All data collected on participants enrolled in the pilot study will be entered into a separate database and will not be analyzed with the data from the main trial. The target enrollment of 2,000 participants for the main trial does not include those participants enrolled in the study pilot.

**Figure 1.** Study Flow Diagram

Recruitment

Screening

Enrollment and Randomization

(Day 1 Visit)

*Hospitalization for all children for 2 days*

Intervention arm

(3 days amoxicillin)

Day 2 Visit

Day 4 Visit

Day 6 Visit

Day 14 Visit

(Study exit)

Control arm

(5 days amoxicillin)

Day 2 Visit

Day 4 Visit

Day 6 Visit

Day 14 Visit

(Study exit)

## Recruitment

Recruitment for this study will be performed by KCH staff during routine intake and screening procedures for the OPD at KCH or BDH. Children between 2 to 59 months of age presenting to the OPDs with cough or difficult breathing will be assessed by hospital staff for potential referral to the study. For any children with a cough fewer than 14 days and chest-indrawing, the clinician will read to the caregiver an ITIP recruitment script (refer to Appendix IV) with a brief introduction to the study. If the caregiver is interested in learning more about the study and in potentially having the child assessed for eligibility, he/she will be referred to study staff.

All KCH staff involved in recruitment procedures will be trained in relevant study-specific procedures and certified in GCP. Each recruitment and referral interaction will be documented for study records.

## Screening

Screening procedures are conducted by study staff to determine eligibility for enrollment in the study. All inclusion/exclusion criteria must be assessed on presentation. The following procedures are performed for screening:

- - Provide information on the study
  - Obtain written informed consent for screening
  - Assign participant identification (ID) number
  - Collect demographic and address information
  - Collect medical history
  - Assess all eligibility criteria, including respiratory rate, chest-indrawing and pulse oximetry assessments (if not already documented in the medical record from that day) as well as a targeted physical examination
  - Perform malaria rapid diagnostic testing (mRDT). Those who are found to have malaria will receive appropriate antimalarial treatment using artemisinin-based combination therapy in addition to the randomly assigned treatment for pneumonia
  - Perform HIV rapid antibody testing if HIV status unknown
  - Perform hemoglobin test (HemoCue®) for anemia

Note that if a child presents with wheezing (audible or auscultatory), study staff will administer a trial of rapid acting inhaled bronchodilator for up to three times, 15-20 minutes apart. Study staff will then assess for fast-breathing and chest-indrawing again to determine the child’s eligibility for this study.

All screening procedures will be conducted by study staff, with the possible exception of the HIV rapid antibody test. HIV testing may be performed by either study staff or a team at KCH or BDH specially trained and experienced in pediatric HIV counseling and testing, whichever will reduce wait times for potential study participants and minimize disruption in regular care provision at KCH or BDH. Caregivers will be informed of all screening results during the screening visit, regardless of the eligibility status of their child.

For those children who are not eligible, study staff will inform the caregiver(s) that their child will not be able to participate in the study and will receive standard care at KCH or BDH instead. Children less than 12 months of age or breastfeeding who are excluded based on an HIV-positive rapid antibody test result will be referred for confirmatory testing (e.g., dried blood spot filter paper test).

All screening procedures will be documented in the appropriate study forms, including logs and case report forms. Clinical assessments and findings will also be documented in the child’s medical record, as appropriate.

## Informed Consent

For the purposes of this protocol, “caregiver” refers to the legally authorized representative (LAR) of the child and informed consent may only be obtained from a child’s LAR. Both mother and father are considered LARs for a child, so consent may be obtained from either parent. In the absence of a biological parent, documented proof of legal guardianship would be needed to establish a caregiver’s status as a LAR.

This study will have two informed consent forms (ICFs): one for screening procedures and one for enrollment procedures. Informed consent is the process of ensuring that caregivers of children fully understand what will and may happen to their children while participating in a research study. Study staff will administer a comprehension checklist to potential participants’ caregivers prior to obtaining written informed consent to ensure that caregivers fully comprehend the nature of the study. The informed consent process continues throughout the study. Key study concepts will be reviewed periodically with the caregivers and the review will be documented. Additionally, if any new information is learned that may affect the caregiver’s decision to stay in the trial this information will be shared with the caregivers in writing. All consent materials will be approved by the appropriate Institutional Review Board (IRB) and Independent Ethical Committee (IEC) prior to use.

Refer to detailed description of informed consent procedures and ethical committee approval in Section 6 (Ethical Considerations and Consent).

## Enrollment Visit

After screening is complete, study staff will perform the enrollment visit procedures for the trial for only those children who are still eligible. For those children who are eligible, the following procedures are performed for enrollment:

- - Administer comprehension checklist
  - Obtain written informed consent for enrollment
  - Perform a physical exam including vital signs and an assessment of any baseline characteristics not already recorded in the medical record or assessed during screening, including measurement of MUAC
  - Collect vaccination history and additional socio-demographic information
  - Collect locator information to be able to contact caregiver and conduct a home visit, if necessary
  - Follow procedures for randomization assignment
  - Provide the participant caregiver with the appropriate study product kits (described below).
    - A study nurse or clinician will prepare and administer the first drug dose, carefully instructing the caregiver how to administer subsequent doses appropriately. The caregiver will receive an instruction sheet with visual and text descriptions of the timing and dosing necessary to complete the treatment regimen. The pharmacists will be unblinded to the randomization allocation, but both provider and caregiver will be blinded to what the child will receive. The amoxicillin DT and placebo DT will appear and taste the same.
    - Children with chest-indrawing will receive amoxicillin DT in two divided doses based on age bands (500 mg/day for children 2 months up to 12 months, 1000 mg/day for children 12 months up to 3 years, and 1,500 mg/day for children 3 years up to 5 years of age) for 5 days (control) or amoxicillin DT in two divided doses based on age bands for the first 3 days followed by placebo DT in two doses for 2 days (intervention).

All enrollment procedures will be documented in the appropriate study forms. Clinical assessments and findings will also be documented in the child’s medical record, as appropriate.

## Randomization

Randomization and enrollment occur at the same study visit, designated Day 1. Randomization is defined as the process of assigning a child to a study arm; assignments are computer-generated by the Protocol Statisticians at UW. The study pharmacists on site will receive the randomization list from the Protocol Statisticians and will be responsible for recording the blinded portion of the randomization code on each study participant’s case report forms and blister pack when they are enrolled and randomized. The list that contains a link between the allocation arm and the study participant ID will be maintained by the study pharmacists under lock and key and/or electronic encryption. Other study staff will not have access to the randomization list.

Children will be randomized to 3 days of oral amoxicillin DT followed by 2 days of placebo DT (intervention) or 5 days of oral amoxicillin DT (control). Treatments will be allocated in a 1:1 ratio. Study investigators and staff will be blinded to all elements of the randomization allocation for the duration of the study.

## Management of Study Participants During Hospitalization

All children enrolled in this chest-indrawing study (ITIP2) will be initially admitted to the hospital for 2 days, to be assessed by study staff for discharge on the morning of Day 3, between 42 and 60 hours after admission. Discharge criteria will be met if none of the criteria for treatment failure are present. Note that due to logistical or social factors (e.g., caregiver not present, lack of transport options at that time of day), some children who meet discharge criteria might not leave the hospital until after the 60 hour window. When confirmed by a study investigator, such children will not qualify as failing treatment, so long as they do not meet any of the other treatment failure criteria.

Children will be primarily managed by study clinicians during any hospitalization, including ward rounds and clinical assessments. Diagnostic tests and medication for intercurrent illnesses will be ordered per ward protocols with results documented in study files. This includes antibiotic treatment regimen changes. To ensure adherence to study protocol, study staff will administer study drugs to participating children during any hospitalization. Study clinicians will be informed by hospital clinicians about the clinical care of children in the study and any clinical decisions made by hospital staff. Study staff will be responsible for orders in the event that study-related laboratory tests and specimen collection are required. In addition to all study staff, all KCH clinicians and nurses will undergo GCP training.

## Follow-Up Visits

Target dates for follow-up visits are calculated from Day 1, the date of randomization. All visits must occur on the calendar day on which they are initially scheduled or within 24 hours afterwards, with the exception for the Day 14 visit, which can occur either 2 days before or after day 14 and still be considered completed within the visit window.

Children will be in the hospital for a follow-up visit on day 2. Caregivers will bring their children for follow-up visits on days 4, 6, and 14.

The Day 2 study visit will occur while the child is still hospitalized for all children admitted for 2 days in ITIP2. Prior to discharge, caregivers will be instructed on how and when to administer the study drug to their child as well as how to contact the study site personnel for concerns that may arise between scheduled visits. Caregivers will receive an instruction sheet with details on the timing and dosing necessary to complete the treatment regimen as well as signs and symptoms that should prompt an immediate call to study staff. A study phone number will be provided to each caregiver and will be answered 24/7.

If a child is not still in the hospital, study staff will attempt to contact the caregiver by phone prior to scheduled study visits to remind them to return to the clinic at the appropriate time.

Follow-up visit procedures at scheduled visits include the following:

- - Review/update locator information
  - Review results from prior visits
  - Collect medical history since the last study visit
  - Perform physical exam including respiratory rate, chest-indrawing and pulse oximetry assessments to assess for treatment failure or clinical relapse
  - For all visits EXCEPT Day 14 visit:
    - Collect study product adherence information from caregiver
    - Review drug dosing and administration procedures with caregiver
  - At the outcome assessment visit (Day 6):
    - Conduct pill counts of study product and document unused amounts
    - Collect all unused study product from the caregiver

For adherence, note that completing 80% of all scheduled dose administrations is considered to meet treatment completion criteria (i.e., 8 out of 10 doses over the 5 days). If doses are missed due to non-adherence, no study action will be taken beyond documenting the missed doses and counseling the caregiver on adherence and study product administration. If a child vomits within 30 minutes of a dose, one repeat dose may be attempted. If a child vomits within 30 minutes after 3 or more scheduled (i.e., not repeat) dose administrations, this will be considered a treatment failure and that child will be referred to care for a work-up of the vomiting cause and will be prescribed a course of second-line antibiotics.

All follow-up visit procedures will be documented in the appropriate study forms. Clinical assessments and findings will also be documented in the child’s medical record, as appropriate.

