**Innovative Treatments in Pneumonia 2**

# BACKGROUND AND INTRODUCTION

The burden of childhood pneumonia remains high, and improved access to effective treatment saves lives. Because vaccines cannot prevent all episodes of pneumonia and because pneumonia incidence remains unacceptably high, there is an urgent need to focus on effective and affordable treatment. Treatment of bacterial pneumonia requires an effective antibiotic used in adequate doses for an appropriate duration. The recommended duration of treatment currently ranges between 5 and 14 days. Shorter duration of therapy, if found to be sufficiently effective, could be particularly important in resource-limited settings where there is a high risk of death, poor access to medicines and health care, and limited budgets for medicines. A shorter antibiotic course is much simpler to administer and is more likely to have improved patient adherence compared to a longer course of treatment when delivered in a community setting. Using a study in Zambia of fast-breathing pneumonia as an example of pneumonia treatment in an outpatient setting, researchers identified only 54% adherence to all doses for 5 days of treatment while observing 76% adherence for 3 days of treatment.[1] Improved patient adherence could also prevent the emergence of antibiotic resistance as well as reduce the rates of adverse events associated with antibiotics. Most importantly, it would reduce the burden on the health systems in resource-limited settings by driving down the costs associated with treatment of childhood pneumonia.

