## SAMPLE SIZE

Refer to Section 5, Statistical Design and Analysis, for more details.

A total of 2,000 children (1,000 per treatment group) will be enrolled. With this sample size we aim to rule out a relative increase in failure rate of 50%. The power of the study to show non-inferiority of the 3-day treatment group at the final analysis when both treatment groups have exactly the same failure rate depends on the failure rate in the standard treatment (5-day) group. The estimated power is adjusted for a 5% loss to follow-up rate in each of the arms. For example, with 1,900 children (950 per treatment arm) for the primary analysis this study has 88% power to show non-inferiority of the 3-day treatment group if the failure rate in both groups is 8% and the non-inferiority margin is a 50% relative increase (which for this failure rate is equivalent to an absolute non-inferiority margin of 4.0%). For this failure rate in the standard treatment group (of 8%), at the final analysis the 95% confidence interval would exclude 12.0%, even if the failure rate is as large as 9.7% in the 3-day treatment group. With 1,900 children with complete outcome data in the primary analysis, the power of this study to show non-inferiority ranges from 64.8% if the failure rates in both groups are 4%, to 96.5% if the failure rates in both groups are 12% (assuming a relative non-inferiority margin of 50% (or equivalently a factor of 1.5). Further details will be provided in the Statistical Analysis Plan (SAP).

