We plan to evaluate treatment with 3 days versus 5 days of oral amoxicillin DT in two divided doses based on age bands (500 mg/day for children 2 months to 12 months, 1000 mg/day for children 12 months to 3 years, and 1,500 mg/day for children 3 years to 5 years of age) among 2,000 children presenting with chest-indrawing pneumonia in a malaria-endemic region of Malawi. Children in the 3-day arm will also receive 2 days of placebo following 3 days of active drug to complete a 5-day course to maintain the blind as to their randomization allocation.

1. **DATA SOURCE**

All study data will be collected by the clinical study staff using designated source documents or electronic case report forms (CRFs). Study data will be entered directly into the electronic CRFs during a study visit. Paper-based versions of all CRFs will also be available for use in the event that electronic data capture is not possible from a technical standpoint. In that case, data will be entered after the fact into the electronic database as promptly as is feasible.

Clinical research data will be maintained through a combination of secure electronic data management system and physical files with restricted access. Triclinium Clinical Trial Project Management (Pty) Ltd. will serve as the contract research organization (CRO) and will be responsible for primary data management activities during the trial. Among other responsibilities, the data management activities include data entry and validation, data coding and cleaning, and database quality control.

Data related to study endpoints will be extracted from the electronic databases for statistical analysis. Two distinct study databases will be available to extract for statistical purposes: the primary study database with study visit data and a safety database with SAE assessments. Statisticians will not have access to any database with participating children’s personally identifiable information.The two study databases containing study endpoint data will identify children only by study identification numbers.

Statisticians will have access to a data download from the web based database at a minimum on a weekly basis.

1. **ANALYSIS SETS/POPULATIONS/SUBGROUPS**

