2. Proportion of children with either treatment failure or clinical relapse before or on day 14 (among all randomized children).
3. Proportion of children with AEs and SAEs.
4. Proportion of children with treatment failure among those testing positive for malaria by rapid diagnostic testing (mRDT) at baseline (overall).
5. Proportion of enrolled children failing treatment among those with wheeze during screening (identified prior to administration of bronchodilators).
6. Proportion of enrolled children failing treatment among those with oxygen saturation <93% by pulse oximetry at baseline.
7. Proportion of children failing treatment among those with MUAC-defined moderate malnutrition (11.5-13.5cm).
8. Proportion of children failing treatment among those with very fast-breathing for age (>70 breaths per minute for 2–11 months, >60 breaths per minute for 12–59 months).
9. Proportion of children failing treatment by age at baseline.
10. **STATISTICAL METHODOLOGY**

*7.1 Design*

The study will include 2,000 children aged 2 to 59 months. Children will be randomized to receive oral amoxicillin for 5 days (control) or 3 days + 2 days placebo (treatment). Treatment will be block randomized (with concealed block size) to ensure a 1:1 ratio of intervention and control. Randomization will be stratified by age group (2 up to 12 months, 12 up to 3 years, 3 years up to 5 years) and site (Bwaila District Hospital and Kamuzu Central Hospital).

*7.2 Interim analysis* We planned two interim analyses after about one-third and two-thirds of children have been enrolled. The seqDesign[2] software was used to determine the appropriate non-inferiority and futility stopping boundaries at each analysis. We assumed a one-sided test with an alpha=0.025, sample size = 1900 (assuming 5% loss to follow-up in each of the arms), a Pocock design for early inferiority and O’Brien-Fleming for early non-inferiority stopping boundaries and a 1.5 relative non-inferiority boundary.

The maximum true failure rates at both the interim analyses and final analysis for the 3-day group for which the 95% CI excludes the non-inferiority margin for various 5-day treatment group failure rates are provided in Table 1 below.

Table 1. Maximum true failure rates for the 3-day treatment arm beyond which stopping for early non-inferiority will be considered

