To account for anticipated loss to follow-up or study withdrawal we will use multiple imputations for any missing outcome data. We will then perform sensitivity analyses to assess how the results might change with varying imputation assumptions. More information is provided in section 8 below.

1. **HANDLING OF MISSING DATA AND OTHER DATA CONVENTIONS**

We have estimated that loss to follow-up or study withdrawal will be 5%. Children lost to follow-up cannot be classified as improved or treatment failures at the missed visit. We will use multiple imputations for any missing outcome data. The imputations will be performed separately for each treatment group and cohort using multiple (20) hotdeck imputations and other information as described below. Multiple imputation estimates will be combined using Rubin’s approach[3].

Specifically, for each episode that is missing outcome data, we will create a subset of episodes that match exactly on treatment arm and gender while matching on age category, highest educational level achieved by the mother (none, primary, secondary, tertiary, while combining these categories for categories with less than 5% of participants, if needed, unknown education level will be multiply imputed, independent from outcome imputation) and adherence information (all combinations of categories for

a) days 1-3: no missing doses, 1-3 missing doses, 4-6 missing doses and

b) days 4-5: no missing doses, 1-2 missing doses, 3-4 missing doses,

unknown dosing information will be conservatively imputed as “not taken” for the 3 day arm and similar to patients where dosing is available for the 5-day arm). We will then randomly select one episode from the corresponding subset with complete information and use its values to replace the entire episode with missing outcome data.

We will repeat this process for each episode missing outcome data and calculate failure rates for both treatment arms using the imputed outcome. We will repeat this 20 times and determine the mean failure rates for each treatment arm. The difference between the mean failure rates will be calculated. Noninferiority bounds as listed in 7.2 will be consulted.

1. **SENSITIVITY ANALYSIS**

We will perform sensitivity analyses to assess how our results might change if the imputation assumptions are changed in a reasonable way, informing the robustness of the primary analysis result. We will perform complete case analysis as one form of sensitivity analysis.

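### The plan has no adherence-based analysis, although the arms differ only in four doses normally given at home; missed control doses would bias toward non-inferiority if 3 days is truly worse

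*Combined protocol and SAP*

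**What the plan says.** The protocol's study product kit table (section 4.7, Table 1) makes the Days 1-3 tablets active in both arms. Only the Days 4-5 tablets depend on allocation. At two doses a day, that is 4 of 10 doses.

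Staff give study drug while a child is in hospital, and discharge is assessed on the morning of Day 3 (section 4.6, Management of Study Participants During Hospitalization). Section 4.6, Follow-Up Visits, states that "completing 80% of all scheduled dose administrations is considered to meet treatment completion criteria (i.e., 8 out of 10 doses over the 5 days". Missed doses lead to documentation and counselling only.

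The SAP section headed "ANALYSIS SETS/POPULATIONS/SUBGROUPS" (section 5) contains eligibility criteria and subgroups but no adherence-based set. The primary analysis compares the randomised arms, with multiple imputation of missing outcomes. SAP section 9 covers changed imputation assumptions and adds: "We will perform complete case analysis as one form of sensitivity analysis". Both kinds of sensitivity analysis address missing outcomes.

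Adherence is collected at visits and by pill count on Day 6. It is reported to the DSMB (protocol section 4.10), and SAP section 8 uses it, split into Days 1-3 and Days 4-5, to match imputation donors. On power, the protocol says: "The estimated power is adjusted for a 5% loss to follow-up rate in each of the arms". It makes no allowance for non-adherence.

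**The concern.** A control child who stops after Day 3 has taken the same active drug as a child in the 3-day arm but is analysed as a 5-day child. In a superiority trial this would cost power. In a non-inferiority trial it favours the conclusion the trial hopes to reach.

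The relative margin adds to the effect. Success means ruling out 1.5 times the control failure rate, so extra control failures both shrink the observed difference and raise the bound. At stake is a claim that 3 days is enough when the comparison was partly 3 days against 3 days. As planned, no analysis would show a reader whether this had happened.

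**Working it through.** **Inputs.**
- Error rate and size, from SAP 7.2: "We assumed a one-sided test with an alpha=0.025, sample size = 1900 (assuming 5% loss to follow-up in each of the arms".
- Analysed number, from protocol section 4.5: "with 1,900 children (950 per treatment arm) for the primary analysis".
- Allocation, from protocol section 4.6: "Treatments will be allocated in a 1:1 ratio".
- Control failure rate 8% and relative margin 1.5, from protocol section 5.1. This gives a bound of 12%, or 4.0 points.
- Assumption, not in the documents: a share s of control children effectively receive none of the Days 4-5 doses and then fail at the 3-day rate.

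**Reproducing the planned power.** With 8% in both arms:
- SE = sqrt(2 x 0.08 x 0.92 / 950) = 0.01245
- Power = Phi(0.04/0.01245 - 1.96) = 89.5%

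Simulating the three looks with the boundaries in SAP Tables 1 and 2 gives 87.5%. Both agree with the stated 88% to within 2 points.

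**What the completion criterion allows.** Two of ten doses may be missed. If both fall on Day 5, that is 2/4 = 50% of the doses that separate the arms.

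**Dilution.** Suppose the true 3-day rate is 12% and the fully taken 5-day rate is 8%, exactly at the margin. The control rate becomes p5 = 0.08 + s x 0.04. A test that allows for estimating the margin uses:
- SE = sqrt(0.12 x 0.88/950 + 2.25 x p5 x (1 - p5)/950)
- P(declare non-inferiority) = Phi((1.5 x p5 - 0.12)/SE - 1.96)

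| s | p5 | bound 1.5 x p5 | SE | P(declare) |
|---|---|---|---|---|
| 0% | 8.0% | 12.0% | 0.0169 | 2.5% |
| 10% | 8.4% | 12.6% | 0.0171 | 5.4% |
| 25% | 9.0% | 13.5% | 0.0175 | 13.5% |
| 50% | 10.0% | 15.0% | 0.0180 | 38.4% |

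**Separating a second issue.** If the upper 95% limit for the difference is compared with 0.5 times the observed control rate, as though that margin were known, the four figures are 5.6%, 10.8%, 23.6% and 54.1%. The excess at s = 0 (5.6% against 2.5%) has nothing to do with adherence, so the table above is the fair measure of dilution.

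**Power of a supportive set.** With 8% in both arms, a fixed 4-point margin as in the protocol's own illustration, and a fraction f of 950 per arm qualifying, power = Phi(0.04/sqrt(2 x 0.08 x 0.92/(950f)) - 1.96):
- f = 90%: 86%
- f = 80%: 82%
- f = 54%: 66%

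With a test that allows for the estimated margin (SE = sqrt(3.25 x 0.08 x 0.92/(950f))), power is lower throughout: 71% for the full set, 67% at f = 90% and 62% at f = 80%.

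**The case against.** The stated aim is to compare two treatment durations, and the combined failure-or-relapse endpoint is specified among all randomised children. A comparison of the randomised arms answers that question, so the lack of a per-protocol analysis is not an error in the primary analysis. This stands.

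The trial also protects adherence. Staff give doses in hospital, caregivers are instructed before discharge, adherence is reviewed at each visit through Day 6, no-shows are visited at home, and pills are counted on Day 6. True non-receipt may be low. This also stands, but none of it is a check within the analysis.

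Four stronger readings are tempting, and the documents do not support them:
- **That the 8-of-10 criterion causes the bias.** No analysis uses it, and dilution would be the same without it. It matters only as a poor threshold for a later per-protocol set.
- **That a drop-off of 29% (1 - 54/76) should be expected.** Protocol section 1 reports that "researchers identified only 54% adherence to all doses for 5 days of treatment while observing 76% adherence for 3 days of treatment". Those were outpatients with fast-breathing pneumonia, and the figures concern taking every dose. They do not show how many doses were missed or when, so they cannot be read as complete non-receipt on Days 4-5.
- **That adherence data serve only imputation.** The DSMB also sees adherence rates.
- **That the claim should require a per-protocol result agreeing in direction and conclusion.** This would turn a supportive analysis into a gate and cost power. With truly equal arms and a random 20% excluded, the two estimates would differ in sign about 15% of the time (arccos(sqrt(0.8))/pi = 0.148).

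**Conclusion.** The point holds as a gap in the supporting analyses. The contrast rests on four doses normally given at home, and no planned analysis looks at whether they were taken. The bias runs toward non-inferiority, and only if 3 days is truly worse. A reader should not infer that non-adherence alone would produce a non-inferior result, or that the primary analysis is wrong.

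On the assumed range, false declaration rises from 2.5% to about 5%, 14% and 38% at 10%, 25% and 50% control non-receipt. These figures assume true rates of 8% and 12%, 950 per arm, complete non-receipt of Days 4-5 in the affected children, failure in those children at the 3-day rate, and a single final look. Partial receipt would give less dilution. The trial's actual position in this range cannot be known from the documents.

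**What to change.** Before unblinding, add to SAP sections 5 and 9 a pre-specified, supportive per-protocol analysis with the same model and margin as the primary:
- Define the set on the Days 4-5 doses, using the split already in SAP section 8, and not on the 8-of-10 total. State the cut-off in advance. The existing middle category (one or two doses missed) still admits a child who missed half of the separating doses.
- Apply the same rule to placebo and active doses, including one rule for unknown dosing. SAP section 8 currently handles unknown dosing differently by arm for imputation.
- Do not count doses due after a treatment failure as missed, so that early failures stay in the set.
- Report Days 4-5 adherence by arm.
- If the result disagrees with the all-randomised result, report and discuss this when interpreting the non-inferiority conclusion. Do not make the claim conditional on agreement.

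The cost is SAP wording and one further run on data already collected. The set is smaller (power about 86% if 90% of children qualify and 82% at 80%, with the margin fixed at 4 points) and is not fully protected by randomisation. Keeping early failures while removing non-adherent children without failure also raises the failure rates and hence the absolute margin. As an upper illustration, if every failure stays and 20% of non-failures are removed, 8% becomes 0.08/(0.08 + 0.92 x 0.8) = 9.8%, and the margin grows from 4.0 to 4.9 points. For these reasons the analysis should support the primary and neither replace nor gate it.
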